**Methods and analysis:**

The PROBE study is a non-randomized controlled intervention study conducted among 600 pregnant women with periodontitis. The women will be recruited among all pregnant women at two Danish hospitals in Region Zealand during their nuchal translucency scan and will subsequently be screened for periodontitis. The intervention group includes 300 pregnant women, who will be offered state-of-the-art periodontal treatment during pregnancy. The control group includes additional 300 pregnant women, who will be offered periodontal treatment after giving birth. Outcome measures include periodontal measures, inflammatory, hormonal and glycaemic markers as well as the prevalence of preterm birth risk, low birth weight and risk markers of gestational diabetes mellitus (GDM) and preeclampsia that will be collected from all screened women and further during pregnancy week 20 and pregnancy week 35 for women enrolled in the intervention.

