## Materials and methods

### Design

Approval was granted by the Committees on Health Research Ethics in the Capital Region of Denmark (journal number H-20083249) on May 19, 2021 and by the Danish Data Protection Agency. The study will be conducted in accordance with the Helsinki Declaration and guidelines for Good Clinical Practice. The study was registered on clinicaltrials.gov (NCT06110143). The PROBE study is a controlled intervention study, where approximately 1200 pregnant women are recruited from Holbaek Hospital and Nykoebing Falster Hospital in Region Zealand in Denmark. About half of the participants are expected to have periodontitis, based on findings from other Nordic countries (1). The recruitment will take place in relation to their appointment for the nuchal translucency scan in gestational week 11–14 followed by a periodontal screening visit with a licensed dentist. The secretaries orally inform all pregnant women attending the nuchal translucency scan about the study. The pregnant women who participate will give informed written consent. Inclusion criteria for the intervention are pregnant women, who speak and understand Danish and are scheduled to give birth and either Holbaek Hospital or Nykoebing Falster Hospital, and are diagnosed with periodontitis (stage I-III) by the study dentist. Exclusion criteria are pregnant women without periodontitis, pregnant women with less than 20 healthy teeth, pregnant women with periodontitis who receives periodontal treatment and pregnant women with periodontitis stage IV.

Data from the Danish Dental Association (2019) indicate that approximately 35% of Danish women (18–39 years) with regular dentist visits have periodontitis. In the same age group, an estimated 65% of the women living in Region Zealand have regular dentist visits. There is no information about periodontitis for those 35%, who do not visit a dentist regularly. Recruitment of pregnant women with periodontitis into the study will last over a period of 18 months for the intervention group and an additional 18 months for the control group. Over a period of 18 month, we expect that approximately 600 pregnant women in the region are eligible for inclusion. Provided half of the invited women accepts the invitation to participate we can include 300 women in each of the two study arms.

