### Statistics

Baseline characteristics of participants will be summarized using descriptive statistics (i.e. means and standard deviations for normally distributed continuous variables, medians and ranges for skewed continuous variables, frequencies and proportions for categorical/binary variables), for both treatment arms and for the total sample. All analyses will be conducted according to the intention-to-treat approach, including all participants, regardless of adherence to the study protocol. The effect of the periodontal treatment performed during pregnancy will be analyzed with regression analyses adjusted for relevant confounders (age, BMI, parity, smoking status, medicine use, socioeconomic status and education level). In addition, statistical analyses (multiple regression analysis, potentially spline analysis) of the changes in hormonal and inflammatory markers in both treatment arms will be performed. To determine the effects of the intervention, time and group-time interaction on outcomes (inflammatory and hormonal markers, glycemic control and periodontitis status), one-way repeated measures ANOVA will be applied. Procedure for testing an interaction effect: If the interaction effect is significant, provide an interpretation of the results, but do not test main effects because the tests for main effects are uninteresting in light of significant interactions. If interaction effects are non-significant, drop the interaction effects from the model and test the main effects. Determining which results to present when testing interactions is often a multi-step process. Statistical software (SPSS, (version 19, Chicago IBM) will be used. A P-value < 0.05 will be considered statistically significant.

All data will be stored in password-controlled databases, and all data will be encrypted. All data collected will be anonymized using a unique study ID. Any identifiable data (e.g. consent forms) will be stored in secure, locked facilities with access limited to the study team.

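### The repeated measures ANOVA for markers, glycaemic control and periodontitis status states no confounders, although the arms are non-randomised successive cohorts, and its main-effect fallback reads cohort differences as treatment effect

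*Protocol article*

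**What the plan says.** The abstract of the protocol article states the design plainly: "The PROBE study is a non-randomized controlled intervention study". Under Design, recruitment "will last over a period of 18 months for the intervention group and an additional 18 months for the control group", so the arms are successive cohorts of volunteers, planned at 300 women each.

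The Statistics section then makes three statements about analysis:

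1. The effect of treatment "will be analyzed with regression analyses adjusted for relevant confounders (age, BMI, parity, smoking status, medicine use, socioeconomic status and education level"). No outcome is named in this sentence.
2. In addition, multiple regression, possibly with splines, "of the changes in hormonal and inflammatory markers in both treatment arms will be performed". No covariates are listed.
3. For the effects of intervention, time and their interaction on a named list of outcomes ("inflammatory and hormonal markers, glycemic control and periodontitis status), one-way repeated measures ANOVA will be applied"), no covariates are listed either.

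A testing sequence follows the third statement. If the interaction is significant, main effects are not tested. If it is not, the interaction is dropped and main effects are tested.

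Under Blood samples, included women are sampled at weeks 11-13, 20-22 and 35-37. The first sample is the baseline one.

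**The concern.** The plan accepts that its arms need adjustment, since it names seven confounders. It then assigns the intervention effect on several outcomes to a model that states none of them. For glycaemic control and periodontitis status, this ANOVA is the only analysis named by outcome. BMI and smoking are on the confounder list and are obvious candidates to influence CRP, IL-6, leptin, insulin and HbA1c.

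Two routes for bias follow if the plan is carried out as written.

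- **The group-by-time term.** It compares within-woman change, so a confounder that shifts the level equally at every visit drops out. A confounder whose association with the marker changes over gestation does not.
- **The main-effect fallback.** Once the interaction is dropped, the group term is a single difference averaged over all visits, including one taken before treatment. Treatment cannot act at that visit, so a genuine effect should appear as an interaction. What the fallback picks up readily is a stable difference between the cohorts, which was there from the start.

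At stake is aim (b), on changes in inflammatory markers, and any claim about glycaemic control or periodontal status.

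**Working it through.** **The plan's own figures.** Table 1 covers only gestational length and birth weight. With 300 or 200 per arm and a two-sided 5% test, (1.96 + 0.84) × SD × √(2/n) gives 2.06 and 2.52 days (stated 2.1 and 2.5) and 129.7 and 158.9 g (stated 130 and 159). The table reproduces, but it has no bearing on the marker models. The documents give no marker SD, between-visit correlation or expected imbalance, so what follows is an illustration.

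**Inputs**
- From the protocol article: n = 300 per arm; three blood samples per included woman; significance at 0.05.
- Assumed: marker SD of 1 at each visit; equal between-visit correlation ρ = 0.6; correlation of one confounder with the marker 0.4; cohort imbalance in that confounder d = 0.1, 0.2 or 0.3 SD; no treatment effect.

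Rejection rate for a bias b with standard error SE: 1 − Φ(1.96 − b/SE) + Φ(−1.96 − b/SE).

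**Group main effect (fallback)**
- SE = √[2 × (1 + 2ρ)/3 / n] = √[2 × 2.2/3 / 300] = 0.0699 SD
- b = 0.4 × d = 0.04, 0.08, 0.12 SD
- Rejection: about 9%, 21% and 40%, against a nominal 5%

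If the confounder shifts only the level, the interaction is non-significant about 95% of the time, so the fallback is the usual path. With equal correlations the two tests are independent, so reaching the fallback and then rejecting has probability 0.95 × 0.40 = 0.38 at the largest imbalance.

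**Group difference in change, baseline to last visit**
- SE = √[2 × (1 − ρ) × 2 / n] = √[1.6/300] = 0.0730 SD
- Confounder shifts level only: b = 0, rejection 5%
- Confounder's slope also changes by 0.2 between the two visits: b = 0.2 × d = 0.02, 0.04, 0.06 SD; rejection about 6%, 8.5% and 13%

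**Range over other assumptions** (300 per arm; b is the bias in marker SD units)

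| b | Main effect, ρ = 0.3 | Main effect, ρ = 0.7 | Change, ρ = 0.3 | Change, ρ = 0.7 |
|---|---|---|---|---|
| 0.05 | 13% | 10% | 8% | 12% |
| 0.10 | 39% | 28% | 18% | 35% |
| 0.20 | 92% | 78% | 54% | 88% |

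At a confounder-marker correlation of 0.4, a main-effect bias of 0.20 SD would need an imbalance of 0.20/0.4 = 0.5 SD in a single confounder, so the last row is an extreme case. The change columns apply only if the confounder biases the change itself by b.

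These figures are for the three-visit blood markers. The Periodontal measures section describes fewer full examinations, so the main-effect formula does not carry over to periodontitis status unchanged.

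**The case against.** The strongest reply is that the text is open rather than wrong. The sentence with the confounders names no outcome, and aim (b) is itself about a treatment effect on markers, so adjusted regression may be meant for them too. A multiple regression of marker changes is planned as well, and that term usually implies several predictors. An article may leave the covariate list of a secondary model to the full protocol or analysis plan.

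Much of this stands. A reader might infer that aim (b) rests solely on an unadjusted ANOVA, or that every marker analysis is unadjusted. The documents do not support either reading: no sentence makes the ANOVA the deciding analysis, and the regression of changes is not said to be unadjusted. A reader might also take 40% as the error rate to expect. It belongs only to the fallback main effect, at the largest imbalance considered and under assumed inputs.

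It might further be argued that each marker's own baseline value must be a covariate. In non-equivalent cohorts, baseline adjustment and change scores rest on different assumptions and can disagree, so the plan is not at fault for using change.

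The reply does not remove the core. The article gives this model's name, its effects and its testing sequence. On the generous reading, an adjusted and an unadjusted analysis address the same marker effects with no statement of which governs. For glycaemic control and periodontitis status, no other analysis is named by outcome. The main-effect fallback is stated outright.

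**Conclusion.** The concern holds in a limited form. The model named to determine the intervention effect on markers, glycaemic control and periodontitis status carries no stated covariates in a non-randomised, sequential design. Its fallback tests a group difference that includes the pre-treatment visit. Followed as written, it can report case mix as treatment effect.

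Under the stated assumptions the false-positive rate is about 9-40% for the fallback main effect. For the change comparison it is 5% if confounding affects level only, and about 6-13% if the confounder's slope also changes by 0.2. These show direction and plausible scale; they do not predict this trial's error rate.

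The point does not extend to the primary outcomes, gestational length and birth weight, which are not in the ANOVA's list. It is worth correcting before analysis. Adjustment deals only with what the listed variables capture; other differences between two recruitment periods would remain.

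**What to change.** - Enter the same seven listed confounders in the repeated-measures model and in the regression of marker changes.
- Base the intervention effect on the adjusted group-by-time contrast, that is, change from baseline. Do not use the group main effect for this, and drop the fallback to it as a test of the intervention.
- Let key confounders such as BMI and smoking have visit-specific effects. This need not apply to every covariate.
- Report the unadjusted ANOVA as descriptive only.
- Adjustment for the marker's own week 11-13 value can be a sensitivity analysis.
- When rewriting the sentence, replace the label one-way: the effects it lists need both a group and a time factor.

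The cost is extra modelling and a rule for missing questionnaire covariates, such as multiple imputation, since women without them would otherwise be lost from the adjusted models. The baseline questionnaire described under Design covers demographics, smoking, medicine use and socioeconomic status. Parity and the woman's own baseline BMI are not listed there by name, so their source should be confirmed.

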### Blood samples

The recruited women will have blood samples collected at either Holbaek or Nykoebing Falster Hospital at the Department of Clinical Biochemistry. Centrifuged and isolated plasma will be stored in Region Zealand Biobank for later analyses. Analyses of the blood samples will be done at Copenhagen Center for Translational Research at the Capital Region of Denmark. Blood will be taken at three time points, at baseline in gestational week 11–13 (from all recruited participants, n = 1200) and in gestational week 20–22 and at gestational week 35–37 from the included women (n = 600).

Inflammatory markers interleukin (IL)- 1β, IL-6, IL-10, IL-17α, (hs-CRP) and tumour necrosis factor (TNF)-α, hormones (insulin, leptin, growth differentiation factor (GDF)-15, adiponectin, resistin) and glycemic markers haemoglobin A1c (HbA1c) will be measured, and the blood samples will be analyzed in one batch at the end of the study to minimize variation. CRP and HbA1c will be measured and analysed on the same day the samples are taken. Saliva samples will be collected at baseline in gestational week 11–13 from all recruited participants and again at gestational week 35–37 from the included women. Procedures are the same for all women in both the intervention and the control group.

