### Power calculation

Statistical power was evaluated prior to commencement of the study using a two-sample means test. Minimal detectible effects for key study outcomes; gestational length (days) and birth weight (g) at 80% power and a significance level at 0.05, assuming 600 (number of enrolled) or 400 participants (200 participants with dropout and/or missing information), are presented below (Table 1).

**Table 1 pone.0302010.t001:** Power calculation.

Outcomes	Expected mean (SD)	Minimal detectable effect (n = 600)	Minimal detectable effect (n = 400)
Gestational length (days)	272 (9)	2.1	2.5
Birth Weight (g)	3490 (567)	130	159

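### In the repeated measures ANOVA, dropping a non-significant group-by-time term and then testing main effects mixes the baseline difference between non-randomised cohorts into the treatment effect

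*Protocol article*

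**What the plan says.** The Statistics section gives the purpose of the repeated measures model: "To determine the effects of the intervention, time and group-time interaction on outcomes", the outcomes being inflammatory and hormonal markers, glycaemic control and periodontitis status. The model is described thus: "one-way repeated measures ANOVA will be applied". A decision rule follows. If the interaction is significant, the analyst is told: "do not test main effects because the tests for main effects are uninteresting in light of significant interactions". Otherwise: "If interaction effects are non-significant, drop the interaction effects from the model and test the main effects". The threshold is stated once for all tests: "A P-value < 0.05 will be considered statistically significant".

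On the visits, the Blood samples section says: "Blood will be taken at three time points, at baseline in gestational week 11–13". The later samples are at weeks 20–22 and 35–37. The baseline sample is taken from all 1200 recruited women; the later two only from the 600 included.

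On the groups, the Abstract calls the study non-randomised. The Design section has the intervention group recruited over 18 months and the control group over a further 18 months, and states: "we can include 300 women in each of the two study arms". Controls are treated after giving birth.

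The Statistics section also plans two other analyses: a regression for the effect of treatment, adjusted for seven named confounders, and a multiple regression (possibly with splines) of marker changes in both arms. It does not rank these against the ANOVA rule.

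**The concern.** When one of the repeated measurements is taken before treatment, treatment can act only on the later ones. Its effect is therefore a difference between arms in change from baseline, which is the group-by-time term. The group main effect is something else: the difference between arms averaged over all visits, including the untreated one. In a randomised trial the baseline part of that average is zero in expectation. Here it is not, because the arms are cohorts from different calendar periods.

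The rule tells the analyst to remove the term that carries the treatment effect whenever it fails to reach 0.05, and then to test the average in its place. A stable difference between the cohorts could then be reported as an effect of periodontal treatment on the markers. These markers serve aim (b) of the study, on systemic inflammation. The rule also allows two tests at 0.05 per marker before any further multiplicity is counted.

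**Working it through.** **The plan's own figures.** The article gives no figure for the repeated measures analysis. Its only calculation is Table 1 ("at 80% power and a significance level at 0.05"), which reproduces with MDE = (1.960 + 0.842) × SD × √(2/n per arm):

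- Gestational length, SD 9 days: 2.06 days at 300 per arm and 2.52 at 200 (stated 2.1 and 2.5).
- Birth weight, SD 567 g: 129.7 g and 158.9 g (stated 130 and 159).

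Table 1 is sound and does not bear on this point.

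**What the group term estimates.** Let d0 be the cohort difference at baseline, and e2 and e3 the treatment effects at weeks 20–22 and 35–37. If the cohort difference is otherwise constant, the differences between arms at the three visits are d0, d0 + e2 and d0 + e3. With the interaction dropped, the group term is their mean:

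d0 + (e2 + e3)/3.

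With e2 = e3 = 0 this is d0. For an outcome with baseline and one follow-up, the same reasoning gives d0 + e/2.

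**Inputs for the size.** From the article: 300 per arm (or 200 after losses), three visits, alpha 0.05. Assumed, because the article gives none: marker SD 1, equal correlation r between visits of 0.4 to 0.7, and constant d0 from 0 to 0.3 SD.

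**No treatment effect, by formula.** The standard error of the group term is √(2(1 + 2r)/(3n)), with n per arm. The chance of passing the interaction step without significance is 0.95.

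- n = 300, r = 0.4: SE = √(3.6/900) = 0.0632. For d0 = 0.1, z = 1.58 and power is 35%; times 0.95 gives about 34%. For d0 = 0.2, z = 3.16 and power is 89%; times 0.95 gives about 84%.
- n = 300, r = 0.7: SE = √(4.8/900) = 0.0730. For d0 = 0.1, z = 1.37 and power is 28%; times 0.95 gives about 26%. For d0 = 0.2, z = 2.74 and power is 78%; times 0.95 gives about 74%.
- n = 200, same formula: about 19–24% for d0 = 0.1 and 58–70% for d0 = 0.2.

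**No treatment effect, by simulation** (2,000 trials per setting, 300 per arm, r = 0.5 or 0.7). Given a non-significant interaction, the group term is significant in:

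| d0 (SD) | Group term significant |
|---|---|
| 0 | 5% |
| 0.1 | 27–31% |
| 0.2 | 78–85% |
| 0.3 | 98–99% |

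With d0 = 0, the rule as a whole gives a significant interaction or group effect in about 9–10% of trials, as 1 − 0.95² = 9.75% predicts. The between-arm difference in change from baseline to week 35 stays at 4–6% for every d0 from 0 to 0.3.

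**Real effect, by simulation** (e2 = −0.1 SD, e3 = −0.2 SD, 300 per arm, r = 0.5). The interaction is missed in about 41–43% of trials. In those trials:

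- d0 = +0.1: the group term averages 0.1 − 0.3/3 = 0 and is significant in 6%.
- d0 = +0.2: it averages 0.2 − 0.3/3 = +0.1 and is significant in the wrong direction in 35%.

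**The case against.** Four points can be made for the plan.

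First, the same section plans a confounder-adjusted regression and a regression of marker changes. A comparison of change between arms is close to what is needed, so a reader who infers that the whole plan discards the treatment effect goes too far. This stands: the fault lies in the ANOVA stream. But the article does not say that the other analyses prevail when they disagree with the rule, and it states no covariates for the ANOVA.

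Second, a reader might infer that the rule tests nothing but the baseline difference. It does so only when there is no treatment effect; otherwise the group term also contains a diluted part of that effect. It is a contaminated average, which is still not a valid estimate of treatment.

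Third, the primary outcomes, gestational length and birth weight, are measured once each. The rule does not reach them, nor does the sample size that rests on them. This stands in full and limits the consequence to aim (b).

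Fourth, the error rates depend on a cohort difference that nobody has observed. That is correct, and nothing in the article shows that one exists. The algebra, however, needs no assumed size, and a non-randomised design with successive recruitment gives no reason to take d0 as zero.

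A separate analysis plan would not dissolve the point, since the article states the rule outright rather than leaving it open.

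**Conclusion.** The rule is wrong as written for the repeated markers. With the interaction dropped, the group term is d0 + (e2 + e3)/3, so a stable cohort difference enters the reported effect of the intervention in full, while the later effects are diluted.

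Under the assumed inputs (300 per arm, r = 0.4 to 0.7, no treatment effect), formula and simulation together put false group effects at about 26–35% for a difference of 0.1 SD and 74–85% for 0.2 SD, somewhat lower at 200 per arm. With no cohort difference the overall error is about 9–10% instead of 5%. A modest real benefit can also be masked or reversed.

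The documents do not support the stronger readings that the trial's primary comparison is compromised, that a cohort difference is known to exist, or that no valid marker analysis is planned.

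**What to change.** Delete the two-step rule. For each repeated marker, state that the treatment effect is the between-arm difference in change from baseline (the group-by-visit contrasts). Estimate and test it whatever the overall interaction p-value, with a 95% CI, adjusted for the confounders the Statistics section already lists. Those covariates must be allowed to act on the change (for example through covariate-by-visit terms), or they leave the contrast untouched. Name this as the governing analysis for the repeated markers, and say that the group main effect is not read as a treatment effect. Which follow-up visit is the main contrast is the sponsor's choice. The label one-way should also go, since such a model has no group factor.

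State the assumption on which the contrast rests: without treatment, the two cohorts would have changed in parallel. This is not guaranteed. If change differed by 0.1 SD for other reasons, the SE of the contrast, √(4(1 − r)/300), is 0.089 at r = 0.4 and 0.063 at r = 0.7, giving about 20–35% false positives. Adjusting the week-35 value for its baseline is not a neutral substitute: with a constant cohort difference of 0.1 to 0.3 SD and no effect, it gave 8–55% false positives at 300 per arm.

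The cost is one paragraph of analysis wording and no new data. In the simulation, the contrast had about 67–69% power (r = 0.5) or 88% (r = 0.7) for a week-35 effect of 0.2 SD at 300 per arm, whatever the baseline difference.

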### The overall rational and aim of the PROBE intervention study is

To determine the effects of the periodontal treatment intervention on a) the risk of preterm birth, low birthweight and markers of preeclampsia and gestational diabetes; and on b) changes in markers of systemic inflammation related to periodontal treatment during and after pregnancy.

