### Periodontal measures

The same study dentist will be performing all the periodontal examinations. Periodontal clinical parameters used to make the periodontal diagnosis are ‘plaque index’ (PI), ‘bleeding on probing (BOP)’, ‘periodontal pocket depth (PPD)’ and ‘clinical attachment loss (CAL)’ and will be measured at baseline (gestational week 11–20), and at gestational week 35–36 in the intervention group. PI will be measured during treatment (up to four treatment sessions before gestational week 35).

PI will be calculated as the mean of the amount of dental plaque present on each tooth. BOP will be calculated as the mean gingival bleeding observed 10 seconds after probing and will be recorded as a percentage. CAL will be measured (in ‘mm’) as the distance from the cemento-enamel junction to the base of the gingival sulcus [30]. PPD will be measured (in mm) as the distance from the gingival margin to the base of the gingival sulcus [30].

As per the clinical definition of periodontitis, a patient will be diagnosed with periodontitis, if a CAL of at least 1 mm is observed on at least two non-adjacent teeth, or a facial/ lingual CAL of at least 3mm is observed on at least two teeth (which may be adjacent) [31]. The observed CAL must not be due to reasons other than periodontitis e.g., traumatic gingival recessions, cervical dental caries, endodontic lesion draining through the marginal periodontium, vertical root fracture or complications associated with the second molar [31]. Periodontitis will further be classified into stages as per the severity of the disease, defined by the worst affected tooth with the highest observed CAL. Due to the lack of radiological diagnosis, CAL, PPD and number of missing teeth, will be the diagnostic criteria for staging periodontitis: StageⅠ(CAL = 1–2 mm, PPD ≤ 4 mm, no missing teeth), StageⅡ (CAL = 3–4 mm, PPD ≤ 5 mm, no missing teeth), Stage Ⅲ (CAL ≥ 5 mm, PPD ≥ 6 mm, 1–4 missing teeth) and Stage Ⅳ (CAL ≥ 5 mm, PPD ≥ 6 mm, ≥ 5 missing teeth) [31].

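### Dropping a non-significant group-time interaction and testing the group main effect on the markers lets a stable pre-existing arm difference be read as a treatment effect

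*Protocol article*

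**What the plan says.** The article describes a non-randomised design: "The PROBE study is a non-randomized controlled intervention study conducted among 600 pregnant women with periodontitis". The arms are formed by calendar time, since recruitment "will last over a period of 18 months for the intervention group and an additional 18 months for the control group" (Design).

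The second half of the aim concerns "changes in markers of systemic inflammation related to periodontal treatment during and after pregnancy". The Blood samples section sets the schedule: "Blood will be taken at three time points, at baseline in gestational week 11–13", then weeks 20–22 and 35–37 in the included women.

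The Statistics section gives the markers a repeated measures ANOVA, with this purpose: "To determine the effects of the intervention, time and group-time interaction on outcomes (inflammatory and hormonal markers, glycemic control and periodontitis status"). If the interaction is significant, it is interpreted and main effects are not tested. If it is not, the instruction is "If interaction effects are non-significant, drop the interaction effects from the model and test the main effects". The threshold is 0.05 throughout.

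The same section also plans, as an addition, "statistical analyses (multiple regression analysis, potentially spline analysis) of the changes in hormonal and inflammatory markers in both treatment arms will be performed". It names no visit for that analysis and does not say which of the two analyses leads. The confounders listed for the regression of the treatment effect do not include the baseline value of the marker.

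**The concern.** When a pre-treatment sample is among the repeated measures, a treatment effect shows as a divergence between the arms over time, which is the interaction. The group main effect answers another question: whether the arms differ on average over all visits, including the one before treatment.

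In a randomised trial, the arms would differ before treatment only by chance. Here the arms are successive cohorts, so a systematic difference in marker level is possible. A difference that stays constant over the visits leaves the interaction null. The rule then passes it to the main-effect test, which is one of the article's stated routes to the effect of the intervention.

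At stake is the marker half of the aim. A difference between cohorts that existed before treatment could be published as an anti-inflammatory effect of periodontal treatment, or could mask a real one.

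**Working it through.** **Plan's own figures.** The article gives no power figure for the markers. Table 1 covers the primary outcomes, with minimal detectable effect = SD × (1.960 + 0.842) × √(2/n per arm).

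- Gestational length, SD 9: 2.06 days at 300 per arm and 2.52 at 200 (stated 2.1 and 2.5).
- Birth weight, SD 567: 129.7 g and 158.9 g (stated 130 and 159).

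Table 1 reproduces. It supplies the two sample sizes used below, 300 and 200 per arm.

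**What the main effect estimates.** Let b be a stable arm difference remaining after any covariates. Let d2 and d3 be the treatment effects at weeks 20–22 and 35–37. The between-arm differences at the three visits are b, b + d2 and b + d3. Their mean is b + (d2 + d3)/3. So b enters in full and the treatment effect only in part.

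**False positives of the fallback.** Assumptions: marker SD 1, equal correlation ρ between visits, no treatment effect, two-sided 0.05.

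- SE of the main effect = √[(2/n)(1 + 2ρ)/3]. At ρ = 0.5 this is 0.0667 for n = 300 and 0.0816 for n = 200.
- The interaction is null, so it is non-significant with probability 0.95.
- Fallback rate = 0.95 × P(|Z + b/SE| > 1.96).
- Worked case, n = 300 and b = 0.10: b/SE = 1.5, main-effect rejection 0.323, fallback 0.95 × 0.323 = 0.307.

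| b (SD) | Fallback, 300 per arm | Fallback, 200 per arm | Change from baseline |
|---|---|---|---|
| 0.05 | 11% | 9% | 5% |
| 0.10 | 31% | 22% | 5% |
| 0.20 | 81% | 65% | 5% |

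For b = 0.10 and ρ from 0.3 to 0.7, the fallback rate runs from 37% to 26% at 300 per arm and from 26% to 19% at 200. A simulation of the full ANOVA rule (2,000 runs per setting, ρ = 0.5) agrees. Its fallback rates for b = 0.10 and 0.20 were 31.6% and 80.6% at 300 per arm, and 22.8% and 65.4% at 200. A change-from-baseline test in the same runs stayed between about 4% and 6%.

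**Both steps with identical arms.** With b = 0 and no effect, 1 − 0.95² = 0.0975.

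**Dilution and power.** Let d be the late effect and f the fraction of it present at week 20–22. The main effect then shows (1 + f)/3 of d: 33%, 50% and 67% for f = 0, 0.5 and 1. Take d = 0.198 SD, the effect for which a baseline-adjusted week 35–37 contrast has 80% power at ρ = 0.5 and n = 300 (SE = √[2(1 − ρ²)/n] = 0.0707). The two-step rule then has 70–86% power over f from 0 to 1, because the interaction step alone already has 57–71%.

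**Candidate replacements at the same d and ρ = 0.5, n = 300.**

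- Change contrast at one visit: SE = √[4(1 − ρ)/n] = 0.0816, power 68%. It removes b entirely.
- Baseline-adjusted contrast: power 80%. It leaves (1 − ρ)b, giving false-positive rates of 6%, 11% and 29% for b = 0.05, 0.10 and 0.20.

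**The case against.** The strongest reply is that the same section already plans a regression of marker changes. A between-group regression of change removes a stable arm difference, and the aim is itself worded as change. Ranking analyses and naming a visit are commonly left to a SAP. This stands as far as it goes, and it makes the repair easy. But the regression is listed as an addition and does not override the ANOVA rule. The fallback is an instruction in the text, not a missing detail.

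Second, b is wholly assumed. The article gives no marker SD, correlation or expected difference. Both arms come from the same hospitals under the same procedures, and stored samples are assayed in one batch at the end, which limits assay drift. That is fair, but CRP and HbA1c are measured on the day of sampling, and batching does nothing about real differences between cohorts.

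Third, the article does not state outright that all three samples enter the model. If baseline were left out, the main effect would be b + (d2 + d3)/2. The dilution would lessen, but b would still pass through in full.

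A reader might infer from the dilution that the plan is badly underpowered for the markers. The figures do not support that, since most real effects of the size considered are caught at the interaction step. Nor should the combined two-step rates (16%, 36% and 86% at 300 per arm) be charged to the fallback: they include the interaction step's own 5%.

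**Conclusion.** The fallback rule is wrong for this design. A group main effect over visits that include baseline, in non-randomised successive cohorts, cannot separate treatment from a pre-existing difference. How often it would mislead depends on b and ρ, which the documents do not give. Across the stable differences examined (0.05 to 0.20 SD, ρ = 0.5), the fallback's false-positive rate is 11% to 81% at 300 per arm and 9% to 65% at 200. The doubling of the error rate to 9.75% needs no arm difference at all. Dilution to at most two thirds of the late effect is real but secondary.

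Two stronger readings should be resisted. A reader might infer that the trial's main result is compromised, but gestational length and birth weight are single measurements and do not go through this rule. A reader might also infer that the arms do differ at baseline. The documents show only that the design permits it.

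**What to change.** Delete the instruction to drop the interaction and test main effects for the markers, and do not report the all-visit group main effect as the effect of the intervention.

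In its place, whatever the interaction p-value, report the between-group difference in change from baseline at weeks 20–22 and 35–37, with confidence intervals, adjusted for the confounders listed in the Statistics section. The planned regression of marker changes can carry this once the visits are named. Give the contrast adjusted for the baseline marker alongside it, and say that it has more power but leaves (1 − ρ) of a stable arm difference.

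This takes two or three sentences and needs no new visits or samples. The price is power: about 68% for the change contrast where the baseline-adjusted contrast has 80% (ρ = 0.5, 300 per arm). The change contrast also removes only a difference that is constant over pregnancy, not one that drifts. Two visits give two contrasts per marker, each at 5%, so the text should say which one leads.
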